## 11.3 Analysis items and methods

　A summary of the statistical analysis is given below. The significance level of the test is set at two-sided 0.05. For details, [name], who is responsible for the statistical analysis, will prepare the first version of the statistical analysis plan before the first patient is enrolled (first patient in), and if necessary, the second version will be fixed before the data are fixed. If a second version is prepared, it will include a history of changes from the first version.

### 11.3.1 Overview of the analysis

1) Composition of the population for analysis

　 The number of enrolled, eligible, treatment-started and analysed subjects will be calculated by intervention group. Subjects who were unable to complete the intervention and those who were found to be ineligible after enrolment will be counted by reason.

2) Subject background factors and baseline data

　 Subject background factors and baseline data such as age, sex and previous medical history will be ascertained and ultrasound imaging will be performed.

### 11.3.2 Hypothesis-testing analysis of primary endpoints

To determine and compare the effects on the tissues surrounding the knee joint before and after the intervention, we will compare the average of each index between the three groups.

If the p-value of this test is less than 0.05 and the mean value of each indicator after the intervention is higher in group M or P than in group C, we judge that the intervention may be useful.

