# 10. target number of people to be registered

　Target number of patients enrolled: 60 (20 in group M, 20 in group P and 20 in group C)

　　Enrolment period: from the date of Ethics Committee approval to 31 January 2024, depending on the subject.

　Duration of the study:from the date of approval by the Ethics Committee to 31 March 2024

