# 11. statistical matters

## 11.1 Basis for setting the target number of people to be registered

To examine the changes before and after the intervention between the three different groups. The rationale for the number of subjects in each group will be based on sample size calculations. Specifically, a two-way analysis of variance will be used for statistical analysis. The number of levels is 1 (before or after the intervention) and the number of groups is 3. Assuming an effect size of 0.4, a significance level of less than 5% and a power of 0.8, the sample size for each group will be calculated to be 52 participants in total. Assuming that there will be a certain number of subjects who declare that they cannot consent to randomisation and who meet the exclusion criteria, we aim to enroll 60 subjects.

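### The success rule in Protocol 11.3.2 contains no test of massage or physical stimulation against control, so when one arm truly differs, an arm with no effect can be called useful

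*Protocol*

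**What the plan says.** Protocol 11.3.2 describes the primary analysis in one sentence: "we will compare the average of each index between the three groups". It then fixes the criterion for success. The p-value of that test must be below 0.05, and "the mean value of each indicator after the intervention is higher in group M or P than in group C". If both hold, the intervention is judged possibly useful; which intervention is not said.

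The rest of section 11 adds little. Section 11.1 says that "a two-way analysis of variance will be used for statistical analysis", and section 11.3 that "The significance level of the test is set at two-sided 0.05". No contrast of M with C or of P with C, no interval and no multiplicity procedure appears in the protocol. Section 11.3.4 on exploratory analysis is marked as not applicable. There are two primary endpoints (section 7.1), and the planned enrolment is "60 (20 in group M, 20 in group P and 20 in group C").

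**The concern.** The trial exists to say whether massage or physical stimulation does more than no intervention. The only inferential element in the rule is a three-group p-value, which is significant whenever any means differ. That includes M differing from P, or one arm falling below control. Once one arm has made the test significant, the other needs only to exceed control by any amount, however small. For an arm with no effect, that is a coin toss.

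The directional check also uses raw after-intervention means, although the stated aim (sections 1 and 11.1) is change from before to after. Chance baseline differences between groups of 20 therefore enter the decision. The two halves of the rule may not even refer to the same quantity, since the p-value can be read as a test of change.

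At stake is the trial's main conclusion, including which of the two interventions it supports.

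**Working it through.** **Inputs from the protocol.** Three groups of 20; two-sided 0.05; effect size 0.4, taken here as Cohen's f because the metric is not named; power 0.8; calculated total 52.

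**Assumptions, not in the protocol.** Normal data with equal SD; one arm shifted by 0.3, 0.8 or 0.85 SD; the other arm identical to control; pre/post correlation 0.5 or 0.7; correlation between endpoints 0 or 0.5.

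**Step 1, the plan's own figure.** Use the noncentral F with λ = N·f² and N − 3 denominator df. With f = 0.4 and 1 numerator df (section 11.1: "The number of levels is 1 (before or after the intervention) and the number of groups is 3"), N = 52 gives power 0.807 and N = 51 gives 0.799, so 52 is reproduced. The three-group test in the success rule has 2 numerator df. Its power is 0.71 at N = 52 and 0.78 at N = 60.

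**Step 2, all arms equal.** The test is significant in 5% of trials. By symmetry, C has the highest mean in one third of these, so M or P exceeds C in two thirds. False declaration = 0.05 × 2/3 = 3.3% per endpoint. Simulation agrees (3.3% to 3.4%).

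**Step 3, one arm differs and the other equals control.** The null arm and C are exchangeable, so the null arm lies above C in half of the significant trials. Its chance of meeting the rule is half the power of the three-group test. For a single-arm shift d, f = d·√(2/9) and λ = 60·f². For change scores, d is divided by √(2(1 − ρ)).

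| Shift | Quantity tested | f | λ | Power | Null arm meets rule |
|---|---|---|---|---|---|
| 0.8 SD | after value, or change with ρ = 0.5 | 0.377 | 8.53 | 0.723 | 36% |
| 0.8 SD | change, ρ = 0.7 | 0.487 | 14.22 | 0.918 | 46% |
| 0.3 SD | after value, or change with ρ = 0.5 | 0.141 | 1.20 | 0.145 | 7% |
| 0.3 SD | change, ρ = 0.7 | 0.183 | 2.00 | 0.216 | 11% |

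The F test ignores sign, so the same figures hold whether the other arm is better or worse than control. Simulation of the full rule agrees.

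**Step 4, both endpoints required.** With the 0.8 SD shift on both endpoints and the endpoints independent: 0.361² = 13% and 0.459² = 21%. With endpoint correlation 0.5, simulation gives 20% to 29%.

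**Step 5, with a test per arm.** Take d = 0.4/√(2/9) = 0.85 SD in M, P null, 20 per arm, one endpoint, no baseline adjustment:

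| Rule | P falsely called useful | Power for M |
|---|---|---|
| Present rule | 39% | 0.77 |
| Three-group test, then pairwise test against C | 2.5% | 0.70 |
| Dunnett (critical t about 2.27) | 1.4% | 0.66 |

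**Step 6, raw after means.** In SD units, the difference between two raw after means has standard error √(2/20) = 0.32. Baseline adjustment multiplies this by √(1 − ρ²), giving 0.27 at ρ = 0.5 and 0.23 at ρ = 0.7.

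**The case against.** Several points on the other side carry weight.

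- **The three-group test does protect against error when nothing works.** This stands (3.3% per endpoint). A reader might infer that the rule controls no error at all; the protocol does not support that.
- **The text names no arm.** If the conclusion means that at least one intervention helps, then with M effective and P null the declaration is true, and 36–46% is not an error rate. This stands. That case is an error only on an arm-by-arm reading. With M worse than control, the declaration is false on both readings.
- **A large harmful effect is remote.** Nothing in the documents suggests that one session of about 10 minutes makes tissue 0.8 SD worse than waiting. At 0.3 SD worse, the figure is 7–11%.
- **The wording may require both endpoints.** If so, 13–29% applies. A reader might take 46% as the size of the problem. That figure needs a large effect, a single endpoint, an assumed correlation of 0.7 and a test on change.
- **The baseline criticism reaches only half the rule.** The planned two-way ANOVA has before/after as a factor, so its p-value can be read as testing change. Only the directional check clearly uses raw after means.
- **Details are left to the SAP, and the claim is mild.** The SAP is not shown and may contain pairwise tests. But the protocol has already fixed the success criterion without them, so an SAP that required them would contradict it. The conclusion is worded cautiously, yet it is the only success criterion under the hypothesis-testing heading.

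**Conclusion.** The point holds in a limited form. As written, the rule never compares M or P with control inferentially. It is sound when all arms are equal and fails when one arm differs.

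For a 0.8 SD difference with 20 per arm, an arm without effect meets the rule in 36% to 46% of trials on one endpoint, or about 13% to 29% if both endpoints are required and both are affected. A one-directional per-arm test would allow at most 2.5%. On one endpoint, the declaration is false under any reading in 36–46% of trials when the other arm is 0.8 SD worse than control, and in 7–11% when it is 0.3 SD worse. The effect sizes and correlations are assumptions. The structural fault does not depend on them, because the null arm's chance is always half the power of the three-group test.

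The use of raw after means is a lesser, related fault. The criterion should be amended before it is applied.

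**What to change.** Reword section 11.3.2 as follows.

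- Judge an arm possibly useful only if its own contrast with control (M−C or P−C) is significant at two-sided 0.05 and in its favour. Name the arm in the conclusion.
- Preferably estimate each contrast on the baseline-adjusted after value, with a 95% CI.
- Control the two comparisons either by Dunnett or Holm, or by pairwise contrasts made only after a significant three-group test. Either choice is adequate with three groups.
- Say whether both primary endpoints must meet the rule.

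The cost is a few sentences and a few lines of analysis code, with no new measurements and no added enrolment. The downside is power per arm. For an assumed 0.85 SD single-arm effect and 20 per arm, it is about 0.66 with Dunnett or 0.70 with gated pairwise tests, against 0.77 under the present rule, before any gain from baseline adjustment. Section 11.1 should state the figure for the chosen contrast in place of 0.8.

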### 11.3.3 Analysis of secondary endpoints

There is a possibility of conducting a backward-looking secondary outcome analysis of the ultrasound images obtained to inform future research activities.

### 11.3.4 Hypothesis exploratory analysis for primary and secondary endpoints

Not applicable.

# 12. completion and submission of the case report form

Not applicable.

# 13. monitoring

Not applicable.

#

# 14. audit

Not applicable.

# 15. ethical matters

## 15.1 Rules to be observed

　All parties involved in this research will comply with the World Medical Association Declaration of Helsinki and the Ethical Guidelines for Medical Research Involving Human Subjects.

## 15.2 Informed consent

　The researcher will provide the subject (including a substitute if one is required; the same applies below) with a consent explanation document approved by the University's Ethics Committee, provide sufficient written and oral explanations, and obtain the subject's free and voluntary consent in writing.

When information that may affect the consent of subjects is obtained, or when changes are made to the implementation plan, etc. that may affect the consent of subjects, the researcher will promptly provide information to the subjects, confirm in advance the subjects' intentions regarding whether or not to participate in the research, and obtain prior approval from the University's Ethics Committee to revise the consent In addition, we will obtain the prior approval of the University's Ethics Committee, revise the consent explanatory document, etc., and obtain the subject's consent again.

The consent document should include the following information

① The name of the research The name of the research and the fact that the research has been authorized by the head of the research institution

② Name of the research organisation and the name of the principal investigator(s). The name of the research institution and the name of the principal investigator (including the name of the joint research institution and the name of the principal investigator of the joint research institution if the research is to be conducted jointly with another research institution)

③ Purpose and significance of the study

④ The method of the research (including the purpose of use of the samples and information obtained from the research subjects) and duration

⑤ Reasons for being selected as a research subject

⑥ Burden and anticipated risks and benefits to research subjects

⑦ The fact that the research subject may withdraw his/her consent at any time even if he/she has consented to the conduct or continuation of the research (if there are cases where it will be difficult to take measures in accordance with the content of the withdrawal from the research subject, etc., a statement to that effect and the reasons therefor)

⑧ A statement that the research subject will not be treated adversely by not consenting to the conduct or continuation of the research or by withdrawing consent.

⑨ How we disclose information about our research

⑩ (ix) The fact that research subjects, etc. may, upon request, obtain or inspect materials related to the research protocol and research methods to the extent that such access does not interfere with the protection of the personal information of other research subjects, etc. and the originality of the research, and the method of obtaining or inspecting such materials.

⑪ Handling of personal information, etc. (including the method of anonymisation, if any)

⑫ Methods of storage and disposal of samples and information

⑬ Status of conflicts of interest relating to the research of researchers and others, including sources of funding for research, conflicts of interest relating to the research of research institutions and earnings of individuals

⑭ Response to consultations from research subjects and related persons

⑮ If there is any financial burden or gratuity to be paid to the research subjects, etc., a statement to that effect and the details thereof

⑯ In the case of research involving medical treatment beyond normal practice, matters relating to other methods of treatment, etc.

⑰ In the case of research involving medical treatment that goes beyond normal medical practice, measures relating to the provision of medical care to research subjects after the research has been conducted

⑱ The results of the research pertaining to the research subject (including incidental findings) if the conduct of the research may lead to important findings concerning the health of the research subject, genetic characteristics that may be passed on to offspring, etc. Treatment of

⑲ In the case of invasive research, the existence and nature of any compensation for damage to health caused by the research

⑳ When there is a possibility that the samples and information obtained from the research subjects will be used for future research that is not specified at the time of receiving consent from the research subjects, etc., or that the information will be provided to other research institutions, that fact and the contents assumed at the time of receiving consent

## 15.3 Protection of personal data

When handling information related to the implementation of the research, a correspondence table will be prepared with numbers unrelated to the personal information of the subjects, and the information will be anonymized to give due consideration to the protection of the confidentiality of the subjects. The correspondence table will be strictly managed by the personal information manager and will not be provided to outside parties. When the results of the research are published, information that can identify the subjects will not be included. In addition, we will not use the information about the subjects obtained in the study for any purpose other than the purpose of the study.

## 15.4 Storage of information, etc.

The ultrasound images and other data relating to this study will be stored under the supervision of the principal investigator and the information (materials) will be stored in a lockable vault in the Department of Physiotherapy, Faculty of Medicine and Health Sciences for 10 years after publication of the results in a paper or other publication. At the end of the storage period, the data will be disposed of in anonymised form. Paper data will be disposed of in anonymised form using a shredder or similar device and electronic data will be completely erased.

# 16. records relating to the provision of samples and information

As no samples or information are exchanged, no records are made.

# 17. changes to the research protocol etc.

　Any changes or revisions to the research protocol or the consent explanatory document for this research must be approved in advance by the University's Ethics Committee.

# 18. costs of research

## 18.1 Research funding and conflicts of interest

This study is funded by the Department of Physical Therapy, to which the principal investigator belongs, and by JSPS Grant-in-Aid for Scientific Research 19K24282. In addition, the researcher in charge of this study shall declare the necessary information to the Shinshu University Conflict of Interest Management Committee for Clinical Research in accordance with the "Procedure for Applying for Ethical Review of Shinshu University School of Medicine", and obtain its review and approval.

## 18.2 Subjects' expenses or gratuities

The equipment used in this study will be provided by the University, so there will be no cost to the subject for participating in the study.

## 18.3 Response to and compensation for health hazards

This is a non-invasive interventional study with no potential for adverse events and will use only the subject's ultrasound images. Therefore, no compensation will be prepared for this study as it is not expected to cause any health problems to the subjects. The approval of the Ethics Committee of the University will be obtained for this matter, and the subjects will be fully informed and asked to participate in this study with their understanding and consent.

# 19. duration of the study and termination/early discontinuation of the study

## 19.1 Research period

　Enrolment period: from the date of Ethics Committee approval to 31 January 2024, depending on the subject.

　　Duration of the study: after passing the ethical review - 31 March 2024

## 19.2 Completion of the study

　The study will be terminated when the data fixation of the last enrolled subject is completed, and the principal investigator will promptly submit a report on the termination of the study to the Medical Director.

## 19.3 Early termination of research

　The Principal Investigator will consider whether or not to continue to conduct the research if any of the following apply

1. If it is judged to be extremely difficult to reach the expected number of subjects due to the difficulty of inclusion
2. the purpose of the research is achieved before the expected number of subjects or the expected duration is reached
3. If the researcher deviates from the ethical guidelines or the research protocol, or breaches a contract, and it is judged difficult to continue the research appropriately.
4. When the University's Ethics Committee instructs changes to the implementation plan, etc., and it is judged to be difficult to accept these changes.

The principal investigator will discontinue the research if the University Ethics Committee recommends or directs that the research be discontinued. When the decision to discontinue the research is made, the researcher will promptly report in writing to the Dean of the Faculty of Medicine with the reasons for the decision.

# 20. storage and use of medical devices and their storage periods

Ultrasound imaging equipment will be used in this study. The ultrasound images and other data relating to this study will be stored under the supervision of the principal investigator and the information (materials) will be stored in a lockable vault in the Department of Physiotherapy, Faculty of Medicine and Health Sciences for 10 years after publication of the results in a paper or other publication. At the end of the storage period, the data will be disposed of in anonymised form. Paper data will be disposed of in anonymised form using a shredder or similar device and electronic data will be completely erased.

# 21. record keeping

The principal investigator will retain important documents related to the implementation of the research, etc. (e.g., copies of application documents, notification documents from the hospital director, copies of various application forms and reports, consent forms, and other documents or records necessary to ensure the reliability of the data) for 10 years after the publication of the results in a paper or other publication. After that, they will be disposed of with care and with respect to personal data.

# 22. publication of research and attribution of results

## 22.1 Registering your research plan

　The study will be registered as a clinical trial in the database of the UMIN Clinical Trials Registration System (http://www.umin.ac.jp/ctr/index-j.htm), which will be updated as appropriate to reflect changes in the study protocol and the progress of the study, and the results of the study will be registered without delay when the study is completed.

## 22.2 Attribution of results

　　The results of this research shall belong to the Faculty of Medicine and Health Sciences, Shinshu University. The principal investigator will publish the results of this study through presentations at relevant conferences.

